#### Sample Size

In this study, the number of participants has been determined statistically. In our hypothesis, the significance level (α) and power (1–β) will be set to 5% and 80%, respectively. Then, an effect size will be calculated using an estimated value of the variability in the MMSE-K and K-MoCA scores based on the literature [26]. As a result, the number of samples came out to be about 10-15 for each group (study or control group) to satisfy the criteria of the normal deviates of significance level and power in the healthy controls and patient groups. The anticipated dropout rate was set to 10%. A similar number of subjects (i.e., 10–15 subjects in each group) can be found in the previous neuroimaging studies [27-29].

#### Study Procedures

All participants will be subjected to measurement of vital signs (blood pressure, pulse rate, and temperature), demographic information, and medical history (past, present, and family). Cognitive function assessments (MMSE-K and K-MoCA) will also be performed during visit 0 (screening). Eligible participants who meet the inclusion and exclusion criteria will receive the schedule for visit 1.

At visit 1, the investigator will check the participant’s vital signs and changes in medication, perform 2 fNIRS scans before and after acupuncture stimulation, and assess the level of CR using CRIq. For medications, the investigator will check for changes but will not specifically allow or restrict certain drugs. According to stratified randomization, the participants will be assigned to 2 acupuncture stimulation groups. Acupuncture stimulation will be performed by a Korean medicine doctor with >3 years of clinical experience. fNIRS scans consist largely of 2 main parts: a 5-minute resting state scan and a task scan of working memory.

#### Cognitive Function Assessment

The investigator will assess 2 cognitive function tests: the MMSE-K and K-MoCA. The MMSE-K is a 30-point questionnaire consisting of 12 questions that are widely used in clinical and research settings to measure cognitive impairment [30]. The K-MoCA is an extensively used 30-point cognitive assessment tool that effectively differentiates MCI [31]. The evaluation of each assessment will be conducted by an investigator blinded to the assigned group.

#### Measurement of Cognitive Reserve

CR assessment will be conducted using the CRIq questionnaire [32]. It includes demographic data and items categorized into 3 sections: education, working activities, and leisure time; each item returns a subscore. It evaluates the CR of an individual by compiling the information associated with the individual’s entire adult life. The quantification of CR will be calculated as the sum of all domains, and the subscore of each domain will also be applied in further correlation analysis. Depending on the mean value of CRIq, it will be dichotomized into the high CR and low CR groups. The investigator will also assess the participants’ bilingualism. The evaluation of each assessment will be conducted by an investigator blinded to the assigned group.

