**Methods:**

This study is a randomized, placebo-controlled trial. Participants without (n=30) and with cognitive impairment (n=30) will be randomly assigned to the verum or sham acupuncture groups. The verum acupuncture group will receive acupuncture stimulation at acupoints related to cognitive function and gain deqi sensation. The sham acupuncture group will receive superficial needling at nonacupoints not related to cognitive function. Each group will undergo cognitive function tests, functional near-infrared spectroscopy imaging before and after acupuncture stimulation, and an assessment of CR. The primary outcomes will be differences in resting brain activities according to disease status, differences in resting brain connectivity before and after acupuncture stimulation between the 2 groups, and changes in brain activity in relation to the CR index. The secondary outcomes will be brain connectivity or network metrics associated with CR and differences in neural activity between the cognitive task and resting states.

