### Outcome Measures

This study aims to explore the immediate neural mechanisms of the acute response to acupuncture stimulation associated with CR in normal aging and disease status and identify the neural substrates of CR.

The primary outcomes will be as follows: (1) differences in brain activation and resting-state brain connectivity according to disease status (the groups with vs without cognitive impairment); (2) differences in brain activation before and after acupuncture between study and control groups (verum acupuncture vs sham acupuncture); and (3) differences in brain activation according to CR (high CR group vs low CR group).

Secondary outcomes are brain connectivity or network metrics (graph theoretic metrics) associated with the CRIq index, differences in brain activity between working memory tasks and resting states, and network metrics associated with cognitive function scores (MMSE-K, K-MoCA).

The brain connectivity matrix will be obtained as Pearson correlation between 48 channels using time-series data during the scan period (Figure 3). Network metrics, including the index of efficiency, clustering coefficient, and centrality, can be calculated using the connectivity matrix by the Brain Connectivity toolbox in MATLAB 2023b (The Mathworks).

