### Statistical Analysis

Only data from participants who completed the fNIRS scan, cognitive function test, and measurement of CR will be contained in the statistical analysis. All categorical data are presented as frequencies or percentiles and will be analyzed using the chi-square or Fisher’s exact test. All numerical data will be presented as the mean and standard deviation and analyzed using an independent *t* test or Wilcoxon rank-sum test. Preprocessing and analyses of fNIRS data will be performed using MATLAB and the NIRSIT analysis tool.

A two-sample *t* test will be performed to compare the brain activations and connectivity between the groups with and without cognitive impairment. A paired *t* test will be conducted to compare the brain activations and connectivity before and after acupuncture stimulation. The CR values from CRIq will be applied for correlation analysis in the form of continuous variables or divided into binary groups (high and low CR) by mean values for subgroup analysis. Since the expression of CR may appear differently depending on the disease status, a subgroup analysis will be conducted by dividing the healthy control and the patient group. Mixed model analysis will be adjusted to determine the interaction effect of intervention and CR in both groups. Pearson correlation will determine the CR-related brain connectivity or clinical score–related metrics. If there is a significant age difference between 2 groups, the age factor will be added as a covariate in the analysis to adjust the effect of age as much as possible.

Statistical significance in fNIRS imaging would be explored using uncorrected and corrected levels (false discovery rate and family-wise error). At the uncorrected level, uncorrected *P*<.001 will be used, and at the corrected level, *P*<.05 will be applied.

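### Primary outcome 3 rests on a high/low cognitive reserve split at an unspecified CRIq mean, and no CR-by-disease comparison is named although differential CR expression is the stated reason for the subgroup analyses

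*Protocol article*

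**What the plan says.** **Form of CR.** Measurement of Cognitive Reserve says: "Depending on the mean value of CRIq, it will be dichotomized into the high CR and low CR groups". It does not say whether the mean is taken over all participants, within each disease group, or from a norm. Outcome Measures lists as the third primary outcome "differences in brain activation according to CR (high CR group vs low CR group". The Abstract (Methods) words the same outcome as "changes in brain activity in relation to the CR index". Statistical Analysis leaves both forms open: "The CR values from CRIq will be applied for correlation analysis in the form of continuous variables or divided into binary groups", with the binary form tied to subgroup analysis.

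**Continuous uses already planned.** On the domain scores: "the subscore of each domain will also be applied in further correlation analysis". Among the secondary outcomes: "Secondary outcomes are brain connectivity or network metrics (graph theoretic metrics) associated with the CRIq index". Pearson correlation is the stated method for these.

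**Disease status.** Statistical Analysis gives a reason, "Since the expression of CR may appear differently depending on the disease status", and the consequence drawn from it: "a subgroup analysis will be conducted by dividing the healthy control and the patient group". The one interaction it names is intervention by CR, in a mixed model, in both groups. Whether those are the disease groups or the acupuncture arms is not clear.

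**The concern.** There are two linked problems.

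First, a primary outcome is defined on a dichotomised score when the score is continuous and is used as such elsewhere in the same plan. Cutting at the mean treats people just above and just below it as opposites, and people far apart on one side as the same. That costs power on a central question of the trial. The unspecified mean adds to this. If it is the mean of the pooled sample, the cut depends on who is recruited, and the high/low label may partly restate disease status and age. Controls may enter from age 19 and patients only from age 60, and CRIq summarises experience over adult life. Age is to be adjusted for only if it differs significantly between two groups.

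Second, the expectation that CR is expressed differently by disease status is a statement about effect modification. The Introduction describes opposite directions: slower decline with high CR in unimpaired people, faster decline with high CR in Alzheimer disease. Two separate subgroup analyses give two results but no comparison between them. Significance in one group and not in the other could be taken for a difference when none exists.

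**Working it through.** **Inputs from the article.** 30 participants without and 30 with cognitive impairment, 60 in all (Abstract); alpha 5% and power 80% (Sample Size; two-sided is assumed here); imaging thresholds of uncorrected P<.001 and corrected P<.05 (Statistical Analysis). The article gives no CRIq distribution, no CR effect size and no power figure for any CR analysis, so there is no stated figure to reproduce. The correlations and distribution shapes below are assumptions.

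**1. Information kept by a mean split.** Relative efficiency is the squared correlation between the score X and the indicator that X exceeds its mean.
- Normal X: 2/π = 0.637, a loss of 36.3%. Effective sample size is 60 × 0.637 ≈ 38 overall and 30 × 0.637 ≈ 19 within a disease group.
- Other assumed shapes: loss of 25% (uniform), 38% (gamma, shape 4), 42% (exponential), 46% (t, 5 df).

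**2. Power.** The correlation that gives about 80% power with continuous CR is r = tanh[(1.960 + 0.842)/√(n − 3)], which is 0.355 at n = 60 and 0.492 at n = 30. Simulation with 20,000 replicates, bivariate normal:

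| n | r | Continuous, 5% | Split, 5% | Continuous, P<.001 | Split, P<.001 |
|---|---|---|---|---|---|
| 60 | 0.355 | 81% | 61% | 30% | 13% |
| 30 | 0.492 | 81% | 60% | 29% | 11% |

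**3. Pooled cut, if that is what is meant.** With two equal normal groups whose CRIq means differ by δ SD, the share labelled high CR is Φ(δ/2) in one group and Φ(−δ/2) in the other. For δ = 0.5 this is 60% v 40%; for δ = 1 it is 69% v 31%. The article does not give δ.

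**4. Two separate subgroup tests when the true correlation is the same.** Power in each group of 30 by Fisher z is p = Φ(atanh(ρ)√27 − c) + Φ(−atanh(ρ)√27 − c), with c = 1.96 for 5%. The chance that exactly one is significant is 2p(1 − p).

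| ρ | p | Exactly one significant |
|---|---|---|
| 0.1 | 0.08 | 15% |
| 0.2 | 0.18 | 30% |
| 0.3 | 0.36 | 46% |
| 0.36 | 0.50 | 50% |
| 0.4 | 0.60 | 48% |
| 0.5 | 0.81 | 30% |

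The 50% at ρ = 0.36 is the mathematical maximum of 2p(1 − p), not a typical value. At P<.001 (c = 3.29) and ρ = 0.36, p = 0.091 and the figure is 2 × 0.091 × 0.909 ≈ 17%.

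**5. What a direct comparison could detect.** The standard error of the difference in Fisher z is √(1/27 + 1/27) = 0.272. The difference detectable with 80% power is 2.802 × 0.272 = 0.76. Power is about 62% for ρ = +0.3 v −0.3 and 88% for +0.4 v −0.4.

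**The case against.** The strongest reply is that CR is not only split. Correlations with continuous CRIq, with its domain scores, and with connectivity and network metrics are all planned. A reader might infer from the dichotomisation sentence that a third of the information is lost throughout. The article does not support that, and the loss must be limited to the primary high/low contrast and the other binary analyses.

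An interaction is also planned, between intervention and CR, so the recommendation there is only about coding CR as continuous. A full list of model terms may properly sit in an analysis plan that is not shown, and no listed outcome is itself a CR-by-disease contrast. It would therefore be too strong to say that the trial will never test the difference, or that subgroup P values will be compared; the article says neither. What stands is narrower. It gives differential expression of CR as its reason for the subgroups, and it names an interaction, but not the one that reason calls for.

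A reader might also take the cut to be the sample mean. The text says only the mean value, so the moving cut and the overlap with disease status remain conditional. Finally, the direct test is not well powered at 30 v 30. That is true, and it argues for reporting an estimate with its interval, not for relying on two subgroup results.

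**Conclusion.** The point holds in limited form. The third primary outcome is fixed as a high/low contrast at an undefined mean, and the Abstract and Statistical Analysis do not agree with that definition. For the binary analyses the cost is about 36% of the information if CRIq is normal, and 25% to 46% under the other shapes tried. At two-sided 5% that takes about 80% power to about 60%. If the cut is a pooled sample mean, high/low CR may also overlap with disease status and age; the article does not settle this.

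No CR-by-disease comparison is named. Under equal true correlations in two groups of 30, a result significant in exactly one subgroup arises in about 15% to 50% of trials at 5% for correlations from 0.1 to 0.5, and in about 17% at P<.001 with a correlation of 0.36. Such a pattern is not evidence that CR acts differently. These figures assume bivariate normal data, a single test and full enrolment. The change should be made, but the defect does not touch the planned continuous CR analyses.

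**What to change.** 1. Define primary outcome 3 on continuous CRIq, and align the Abstract, Measurement of Cognitive Reserve, Outcome Measures and Statistical Analysis with it.
2. Fit one model over all participants with CRIq, disease group, CRIq by disease group, and age.
3. Use continuous CRIq in the intervention-by-CR mixed model that is already planned.
4. Report the CRIq-by-disease interaction with its confidence interval. State that at 30 v 30 only a large difference, about 0.76 on the Fisher z scale, is detectable with 80% power. Present the subgroup estimates as description.
5. Keep the high/low split for display only, and say whose mean defines it.

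The analysis change is small, but it redefines a primary outcome in a registered trial that had already enrolled 50 participants. It therefore needs an amendment reported to the IRB and entered in the registry, made before the outcome data are analysed. No new data or participants are needed.

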#### fNIRS Imaging

For this experiment, fNIRS equipment (NIRSIT, OBELAB) will be used. fNIRS is a portable near-infrared neuroimaging device that measures hemodynamic variations in cerebral blood by irradiating the cerebral cortex with a near-infrared laser. The equipment irradiates the wavelengths of 780 and 850 nm of laser, which is harmless to humans. It contains 48 channels that can cover the frontal regions of the brain, allowing the quantification of ΔHbO_2_, ΔHbR, and ΔHbT in that area. Based on this, the analysis applied in fMRI, such as graph theory analysis and general linear model analysis, can be used.

The fNIRS scans will be conducted before and after acupuncture. The scan consists of 2 parts: a resting state and working memory task scan. The resting-state fNIRS scan lasts for 5 minutes, during which the participant is asked to look at the monitor screen and remain comfortable. The task fNIRS scan is performed while conducting a Corsi block tapping task, a cognitive task related to working memory [33]. This experiment requires participants to tap a spatially separated sequence of up to 9 identical blocks in the same order in which they are presented. The sequences start simple, using 4 blocks, and become more complicated using a maximum of 6 blocks (Figure 2).

**Figure 2 figure2:**
[figure not shown]
Presentation of Corsi block task.

### Interventions

In the study group, verum acupuncture stimulation will be conducted for 15 minutes by stainless steel acupuncture (0.25 mm×40 mm, Dongbang acupuncture) on acupoints, which are known to be associated with cognitive functions in previous studies (Baihui [GV20], Sishencong [EX-HN1], Taixi [KI3], Zusanli [ST36], Hegu [LI4], and Taichong [LR3]), and deqi sensation will be induced [24,34,35]. The needle will be lifted and thrust approximately 30-50 mm and twisted and rotated at approximately a 90°-180° angle 60 times/minute (60 Hz). The manipulation will then be performed at 1-minute intervals to maintain the amount of stimulation and achieve deqi sensation. A questionnaire on deqi sensations will be implemented.

For the control group, superficial needling acupuncture (depth of needling: 1-2 mm per nonacupoint) will be performed for 15 minutes using stainless steel acupuncture (0.25 mm×40 mm, Dongbang acupuncture) on nonacupoints. Nonacupoints, which are not related to cognitive function, would be approximately 1 cm away from the acupoints of the study group. The needles for sham acupuncture will remain in place. In the case of superficial needling, manipulation techniques and induction of deqi sensation will not be achieved.

Superficial needling can be a subtype of minimal acupuncture [36]. We thought that the characteristics of acupoints, depth of acupuncture stimulation, intensity of the stimulation, and deqi sensation would all be determinants of acupuncture stimulation. Therefore, we selected minimal acupuncture that lacks these features as a sham control. This type of sham acupuncture has been applied in various studies, including Bell’s palsy, migraine, and chronic musculoskeletal pain syndrome, for a long time [37-40].

### Outcome Measures

This study aims to explore the immediate neural mechanisms of the acute response to acupuncture stimulation associated with CR in normal aging and disease status and identify the neural substrates of CR.

The primary outcomes will be as follows: (1) differences in brain activation and resting-state brain connectivity according to disease status (the groups with vs without cognitive impairment); (2) differences in brain activation before and after acupuncture between study and control groups (verum acupuncture vs sham acupuncture); and (3) differences in brain activation according to CR (high CR group vs low CR group).

Secondary outcomes are brain connectivity or network metrics (graph theoretic metrics) associated with the CRIq index, differences in brain activity between working memory tasks and resting states, and network metrics associated with cognitive function scores (MMSE-K, K-MoCA).

The brain connectivity matrix will be obtained as Pearson correlation between 48 channels using time-series data during the scan period (Figure 3). Network metrics, including the index of efficiency, clustering coefficient, and centrality, can be calculated using the connectivity matrix by the Brain Connectivity toolbox in MATLAB 2023b (The Mathworks).

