Acupuncture has been practiced for thousands of years as an important treatment for a variety of diseases in East Asian medicine [16,17]. It is also being explored in AD research as a complementary and alternative therapy. In a meta-analysis, acupuncture treatment alone showed acceptable efficacy compared to conventional medicine for the management of AD. In addition, in a randomized controlled trial in patients with mild to moderate AD, acupuncture was found to be safe, well tolerated, and effective in improving cognitive function and global clinical status [18]. Specifically, acupuncture has been shown to regulate the release of central neurotransmitters, including acetylcholine and monoamine neurotransmitters [19]. Current neuroimaging studies of acupuncture cover a variety of diseases ranging from pain-related diseases such as chronic low back pain to peripheral and central nervous system disorders including carpal tunnel syndrome, stroke, Parkinson’s disease, and dementia [20-24]. Through these, the analgesic mechanism and neuroprotective effect of acupuncture, which are distinct from sham needling, are consistently elucidated. Among them, a systematic review dealing with 13 AD-related neuroimaging studies found that acupuncture may modulate the default mode network, the central executive, and the frontoparietal networks in the brains of AD patients [24]. However, on the macroscale, the acute neural mechanisms of acupuncture stimulation in relation to CR according to disease status are largely unknown. To identify the neural mechanisms of acupuncture stimulation associated with CR in healthy aging and cognitive impairment patients, rigorous clinical trials such as randomized, placebo-controlled trials with neuroimaging techniques are required.

In this study, our main hypothesis would be that brain networks and brain activations focused on frontal regions would be altered according to the disease status and CR level, and that brain connectivity in the frontal regions would change before and after acupuncture stimulation. Next, we aim to investigate the neural substrates of CR and cognitive function using network metrics. Herein, we present a protocol for a randomized, placebo-controlled, parallel-group clinical trial to explore the acute neural changes after acupuncture stimulation according to CR and elucidate the neural substrates of CR according to disease status by applying fNIRS.

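### The primary outcome for verum versus sham acupuncture is resting brain connectivity in the abstract but brain activation in Outcome Measures, and nothing in the document reconciles the two

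*Protocol article*

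**What the plan says.** All references are to the protocol article.

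- **Abstract, Methods.** The second primary outcome is "differences in resting brain connectivity before and after acupuncture stimulation between the 2 groups".
- **Outcome Measures.** The second primary outcome is "differences in brain activation before and after acupuncture between study and control groups", verum against sham. Connectivity is primary only in the first outcome, which is not randomised: "differences in brain activation and resting-state brain connectivity according to disease status". On the secondary side, connectivity appears through its link to cognitive reserve: "Secondary outcomes are brain connectivity or network metrics (graph theoretic metrics) associated with the CRIq index". Network metrics also appear in relation to the cognitive scores. Change in connectivity with acupuncture is not listed at either level.
- **Introduction, last paragraph.** Part of the main hypothesis is that "brain connectivity in the frontal regions would change before and after acupuncture stimulation". It does not say at rest, and it does not mention the sham arm.
- **Figure 3 caption.** It presents resting-state connectivity matrices from either side of the stimulation.
- **Statistical Analysis.** Paired before-after tests are planned for activation and for connectivity, with neither called primary.

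The other two primaries also vary in wording. For disease status, the abstract speaks only of activity at rest, while Outcome Measures has activation plus resting-state connectivity. For cognitive reserve, the abstract has "changes in brain activity in relation to the CR index" and Outcome Measures has "differences in brain activation according to CR (high CR group vs low CR group").

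**The concern.** Verum against sham is the only contrast that randomisation protects, so its primary outcome is the one that most needs a single definition. Here a reader of the abstract and a reader of Outcome Measures would expect different results to be headlined. The abstract's primary outcome does not appear in the Methods list at all. A report built on either measure could cite this article as its pre-specification, and a reader could not tell whether the choice came before or after the data.

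The choice also changes the statistics. Activation is assessed by channel and connectivity by channel pair, so the number of tests, the correction needed and the detectable effect all depend on which measure is meant.

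**Working it through.** **1. Are these two names for one measure?** No. Outcome Measures lists activation and resting-state connectivity side by side in its first primary outcome. Statistical Analysis also names them separately. Connectivity is defined as a Pearson correlation between channel time series, which is not a channel-level activation.

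**2. Does another section settle it?**
- The hypothesis and the Figure 3 caption point to connectivity, but the hypothesis gives neither the scan condition nor the arm contrast.
- Statistical Analysis covers both measures and ranks neither.
- Sample Size could have shown which measure was intended. Its inputs are 5% significance, 80% power and the variability of MMSE-K and K-MoCA scores, giving about 10–15 per arm. No difference, standard deviation or effect size is stated, so this figure cannot be reproduced. Solving backwards, assuming a two-sided test and equal arms, d = (1.960 + 0.842) × √(2/n). This gives d = 1.25 at n = 10 and d = 1.02 at n = 15. Neither value is tied to an fNIRS measure, so the calculation does not identify the primary.

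**3. Size of the test families.** With 48 channels (fNIRS Imaging and Outcome Measures), for one haemoglobin signal:
- activation: 48 tests;
- connectivity: 48 × 47 / 2 = 1128 tests.

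At the uncorrected threshold in Statistical Analysis (P<.001), if there were no true effects:
- expected false positives: 48 × 0.001 = 0.048 against 1128 × 0.001 = 1.13;
- chance of at least one, if tests were independent: 1 − 0.999^48 = 4.7% against 1 − 0.999^1128 = 67.7%.

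Channel pairs share channels and are not independent, so the last two percentages show scale only. The expected counts do not need independence.

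**4. Cost of an open choice, as an illustration.** Assume each measure is reduced to one two-sided test at 5% and either may be called primary.
- Independent tests: 1 − 0.95² = 9.75%.
- Correlated test statistics (bivariate normal simulation): about 9.5%, 9.1% and 7.8% at correlations of 0.3, 0.5 and 0.8.
- One measure fixed in advance: 5%.

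**The case against.** The strongest reply has four parts.

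*The study is exploratory and both analyses are declared.* Outcome Measures does describe an exploratory aim, and Statistical Analysis commits to testing both measures. But the article labels these outcomes primary, states a main hypothesis and sets 5% significance and 80% power. Declaring both tests does not say which one carries the primary claim.

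*The registration and protocol V.1.0 may fix the endpoint.* They may, and neither is shown. That matters for how the repair is made. It does not remove the conflict, because any single definition still contradicts one section of this article.

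*Changing an endpoint this late is itself a risk.* This stands in part. Results reports 50 participants enrolled of the 60 planned, with recruitment ending in February 2025. It argues for returning to the approved version and against picking a measure afresh.

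*Some apparent contradictions are weaker than they look.* This also stands.
- A reader might infer that the main hypothesis already names the verum-sham difference in resting connectivity as primary. It does not: it mentions neither rest nor the sham arm.
- A reader might take activation to mean the task response and conclude that the two measures come from different scans. The article never defines activation that way, and the abstract refers to activity at rest.
- The continuous and high/low uses of the CRIq are both declared in Measurement of Cognitive Reserve and in Statistical Analysis. They are two planned analyses, and what is missing is which one is primary.

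**Conclusion.** The contradiction is confirmed in the current text. For the randomised comparison, the abstract and Outcome Measures name different primary measures, and the abstract's measure appears nowhere in the Methods outcome list for that comparison. This should be corrected before the final analysis.

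The firm quantity is the difference in test families, 48 against 1128 per haemoglobin signal. The 9.75% is an upper illustration that rests on two independent single tests at 5%. It is not this trial's error rate, because the plan uses uncorrected P<.001 or corrected P<.05 across many channels or pairs.

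A reader might also infer that the investigators mean to choose the endpoint after seeing results. The document says nothing of the kind; the point is only that the text as it stands would not prevent it. Nor does the document support the conclusion that connectivity must be the right primary.

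The variation in the disease-status primary and the unranked CRIq analyses are lesser matters of consistency that can be settled in the same amendment.

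**What to change.** Before the final analysis, and reported to the IRB as Quality Control requires for important modifications:

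1. State one measure, activation or connectivity, as the primary outcome for the verum-sham difference in before-after change, and say whether it comes from the rest or the task scan. Follow the originally approved protocol version where it settles the point. Where it does not, record the decision, its date and that it preceded the analysis.
2. Use the same wording in the abstract, the hypothesis, Outcome Measures and Statistical Analysis.
3. List the other measure as secondary for the same contrast.
4. Word the disease-status primary identically in the abstract and Outcome Measures.
5. Say which of the two declared CRIq analyses, continuous or high/low, is primary.

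No new data are needed. The cost is a late but documented amendment, and one of the two measures will be reported as secondary.
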